#### Maximal respiratory pressures

Maximal inspiratory (MIP) and expiratory (MEP) pressure will be assessed with a respiratory pressure meter (MicroRPM, MicroMedical Ltd., Kent, UK). All measurements will be performed with the participant seated, using a 2-mm aperture mouthpiece and a nose clip to prevent air leakage. MIP will be measured from residual volume, whereas MEP will be measured from total lung capacity. Clear instructions about performing the test will be provided [31].

#### Flowmeter

While the patient is seated, a mini-Wright flowmeter (Clement Clarke, Mason, OH, USA), nosepiece, and disposable nozzle will be used to measure peak expiratory flow. Peak expiratory flow measurement will be based on maximum inspiration. After being instructed the use of the flowmeter, the patients will be asked to blow as hard and as long as possible [32].

#### Hand dynamometry

To evaluate handgrip strength, a digital dynamometer will be used (CAMRY EH101, Guangdong, China). After being instructed about the test and use of the dynamometer, the participants will perform a maximal isometric contraction for 5 s with each hand while standing [33].

#### Six-minute walk test

The 6-min walk test will be used to evaluate functional capacity. It will take place in a flat corridor with a 15-m track. A cone will be placed at each meter to determine the beginning and ending distance. Participants will be instructed to walk back and forth as quickly as possible for 6 min, and the total distance covered during will be recorded. Before and after the test, blood pressure, heart rate, and oxygen saturation values will be measured. Verbal encouragement will be given every minute, according to Mexican National Institute of Respiratory Disease guidelines [34].

#### Perceived quality of life

The Moorehead-Ardelt quality of life questionnaire II will be applied at each evaluation, and the Bariatric Analysis and Reporting Outcomes System (BAROS), which has been validated for bariatric surgery patients, will be applied at the final evaluation [35, 36].

#### Moorehead-Ardelt quality of life questionnaire II

This test measures quality of life in 6 dimensions: self-esteem, physical activity, social activity, work activity, and sexual activity. Each dimension has 10 response options that are accompanied by images for clarification. Each answer is scored through a visual scale ranging from − 0.5 (most unfavorable situation) to + 0.5 (most favorable situation). The sum of all dimensions produces a global score: very good (2.1 to 3), good (1.1 to 2), fair (− 1 to 1), poor (− 2 to − 1.1), and very poor (− 3 to − 2.1).

#### Bariatric analysis and reporting outcomes system

This test measures quality of life and the benefits of bariatric surgery by incorporating the weight loss or gain percentage after surgery into the Moorehead-Ardelt questionnaire, including comorbidity resolution, reoperation, and complications. While the Moorehead-Ardelt scoring is identical to that described above, the other items are scored according to dimension. Scores for the weight loss dimension (as percent of excess weight lost) were as follows: − 1 (0–24%), 0 (25–49%), 1 (50–74%), and 2 (75–100%). Scores for the comorbidities dimension were as follows: − 1 (aggravated), 0 (no changes), 1 (some improvement), 2 (one major comorbidity resolved and improvement in others), and 3 (all major comorbidities resolved and all others improved). Scores for the complications dimension were as follows: deduct 0.2 points for a minor complication, deduct 1 point for a major complication, and deduct 1 point for reoperation. Global scores for the instrument are the sum of all dimensions, categorized as failure (≤ 1), fair (> 1 to 3), good (> 3 to 5), very good (> 5 to 7), and excellent (> 7 to 9).

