**Discussion:**

Both exercise protocols in this study were developed according to evidence-based practice. It is expected that, after 16 weeks of intervention, body composition (measured by electrical bioimpedance), cardiopulmonary function (measured by heart rate variability, maximal inspiratory pressure, maximal expiratory pressure, peak expiratory flow, handgrip strength, and the 6-min walk test), and perceived quality of life (measured by the Moorehead-Ardelt quality of life questionnaire II and bariatric analysis and reporting outcome system scores) will improve, especially in the HIIT group.

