### Outcomes {12}

Outcomes will be assessed at four time points: (1) 1 week before surgery, (2) 21 days after surgery (baseline before starting the exercise program), (3) 8 weeks after the beginning of the exercise program, and (4) 1 week after the end of intervention.

Primary outcomes will be (1) body composition, (2) heart rate variability, (3) 6-min walk test results, and (4) perceived quality of life. Secondary outcomes include the results for (1) maximal respiratory pressure, (2) flowmeter, (3) hand dynamometry, (4) the 30-s sit-to-stand test, and (5) the basal metabolic rate.

Data collection will include sex, age, place of residence, marital status, education level, and physical activity level according to the International Physical Activity Questionnaire [29].

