## Statistical methods

### Statistical methods for primary and secondary outcomes {20a}

Data normality will be assessed with the Shapiro-Wilk test. Variance homogeneity and sphericity will be assessed with the Levene and Mauchly tests, respectively. For the primary and secondary outcomes that meet the assumptions for the analysis of variance (ANOVA), a mixed model ANOVA with Bonferroni correction will be used to assess the interaction between group (control group vs MICT vs HIIT) and time (baseline vs post 8-week intervention vs post 16-week intervention). Otherwise, data will be analyzed with the Wilcoxon test for within-group comparisons and the Mann-Whitney test for between-group comparisons using the Bonferroni’s correction. The significance level will be set at 5%. Cohen’s *d* will be calculated to determine the effect size. All analysis will be performed in SPSS 24.

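### The BAROS scoring rules sum to 8 on a scale that ends at 9, and BAROS, collected once, cannot enter the planned group-by-time model

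*Protocol article*

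**What the plan says.** Outcomes {12} in the protocol article gives the last two primary outcomes as "3) 6-min walk test results, and (4) perceived quality of life". The abstract's discussion paragraph says that quality of life is "measured by the Moorehead-Ardelt quality of life questionnaire II and bariatric analysis and reporting outcome system scores".

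The section on the Moorehead-Ardelt questionnaire states: "This test measures quality of life in 6 dimensions: self-esteem, physical activity, social activity, work activity, and sexual activity". Each dimension scores from −0.5 up to "0.5 (most favorable situation", and the global categories run from −3 to 3.

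The BAROS section carries the questionnaire score over unchanged and adds three components:

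- **Weight.** The item is described as covering both loss and gain. The codes are −1 for 0–24% of excess weight lost, then "0 (25–49%), 1 (50–74%), and 2 (75–100" per cent.
- **Comorbidities.** Codes run from −1 (worse) through 0 (unchanged) to 3.
- **Complications and reoperation.** These only deduct points.

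The global score adds all components. The categories are failure (1 or less), fair (above 1 to 3), good (above 3 to 5), very good (above 5 to 7) and "excellent (> 7 to 9".

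On timing, the section Perceived quality of life gives the questionnaire at every evaluation. Of BAROS it says "which has been validated for bariatric surgery patients, will be applied at the final evaluation".

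Statistical methods {20a} plans one route for all primary and secondary outcomes: a mixed ANOVA for the interaction of group with "time (baseline vs post 8-week intervention vs post 16-week intervention". If the ANOVA assumptions fail, Wilcoxon tests are used within groups and Mann-Whitney tests between groups, with Bonferroni correction.

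**The concern.** A scoring table should be able to produce every value on the scale it feeds. Here the printed item codes cannot reach the printed top of the scale, and one situation that the text names, weight gain, has no code. Staff who follow the table as written will produce totals that may not fit the categories printed beside them. The failure-to-excellent classification of participants would then be unreliable.

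The analysis problem is separate. BAROS is part of a primary outcome, but the model assigned to primary outcomes needs repeated measurements and BAROS has one. The protocol also does not say which of the two scores is the quality-of-life variable for that model. The choice of variable and test would therefore be made after the data are in.

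**Working it through.** **Inputs**, all from the questionnaire and BAROS sections of the protocol article:

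| Component | Lowest code | Highest code |
|---|---|---|
| Each questionnaire dimension | −0.5 | +0.5 |
| Weight loss | −1 | 2 |
| Comorbidities | −1 | 3 |
| Complications, reoperation | deductions | 0 |

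**Step 1: questionnaire range.** Six dimensions give 6 × 0.5 = 3 and 6 × (−0.5) = −3, which reproduces the stated range. The five named dimensions would give only 5 × 0.5 = 2.5. The count of six is therefore right and one name is missing from the list.

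**Step 2: BAROS maximum.** 3 (questionnaire) + 2 (weight) + 3 (comorbidities) + 0 (complications) = 8. The stated upper limit is 9, so it is not reproduced. Totals above 8 cannot occur, and the top category in effect runs from above 7 to 8.

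**Step 3: where the missing point could lie.** Suppose each weight-loss code were one point higher: 0, 1, 2, 3 for the four bands. The maximum becomes 3 + 3 + 3 + 0 = 9, and −1 is freed for weight gain. That would also match the comorbidity item, where −1 means worsening and 0 means no change. This is an inference. The limit of 9, or another item, could equally be the misprint.

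**Step 4: consequence if the weight codes are one point low (assumption).**

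- Example: questionnaire +1, comorbidities 1, 60% of excess weight lost, no complications. As printed, 1 + 1 + 1 = 3, which is fair. With the higher code, 1 + 1 + 2 = 4, which is good.
- The 56–85% first-year excess weight loss cited in the Background would be coded 2 to 3 rather than 1 to 2.
- Fair, good and very good are each 2 points wide, so a 1-point shift is half a category. If totals were spread evenly within categories, about half of participants would move. The protocol gives no distribution, so this is only an illustration.

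**Step 5: effect on comparisons between arms under the same assumption.** Everyone with 0–100% of excess weight lost gains the same point. The mean difference is (A + 1) − (B + 1) = A − B. Standard deviations, and hence Cohen's d, are unchanged, and so is the rank order.

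**Step 6: time points.** The ANOVA needs three occasions: baseline, 8 weeks and 16 weeks. BAROS supplies one. Neither a time effect nor a group-by-time interaction can be estimated, and a within-group Wilcoxon test has no second measurement to pair. A Mann-Whitney comparison at one visit is possible, but the plan triggers it by failed ANOVA assumptions, not by a single measurement.

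**The case against.** Much can be said in the plan's defence, and several stronger readings that a reader might draw do not hold.

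- **That every BAROS total is one point too low.** The documents show only that 8 is not 9. They do not show which entry is wrong, and the cited instrument is not available here. The uncoded weight gain makes the weight item the likeliest source and no more. This objection stands.
- **That the trial's comparisons are biased.** A uniform shift changes no mean difference, rank test or Cohen's d, and {20a} plans no analysis of category counts. This stands for the shift in Step 5. It would not automatically hold if a different item were at fault, because the error might then not be the same for everyone.
- **That part of a primary outcome has no usable test.** Mann-Whitney is named in {20a} and suits a single-visit score. This stands in part: the tool is there, but the stated rule does not lead to it when assumptions are met.
- **That the questionnaire might be scored on five items.** The stated count of six and the range of −3 to 3 both rule this out. The omission is a listing slip.
- **That collecting BAROS once is itself an error.** It is not. A single postoperative assessment is legitimate, and the defect is the mismatch with the model.

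One could add that an article leaves scoring and analysis detail to fuller documents. That excuses omissions. It does not excuse printed figures that contradict each other, or a stated model that cannot be fitted to a named outcome.

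**Conclusion.** The point holds as an internal inconsistency of moderate weight. Two things are certain from the protocol alone: the printed BAROS items reach 8 on a scale ending at 9 with no code for weight gain, and a score taken once cannot enter a three-occasion group-by-time model.

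The one-point understatement is conditional on the weight item being the source. If it is, the harm is to category assignment, by half a category width, and not to mean or rank comparisons between arms. How many participants would change category cannot be worked out from the documents.

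The matter is more than clerical because the scoring table generates part of a primary outcome, and the analysis sentence for that outcome needs a decision before the data are examined.

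**What to change.** 1. Before scoring, check the weight-loss codes (including weight gain) and the category limits against the cited instrument, and correct whichever entry is wrong so that the items sum to the stated upper limit. Rescore any items already collected.
2. Name the Moorehead-Ardelt total, measured at every visit, as the quality-of-life variable for the group-by-time model.
3. State that BAROS is compared between the three groups at the final visit only. One-way ANOVA or Kruskal-Wallis would do. So would ANCOVA on the Moorehead-Ardelt score from the visit 21 days after surgery, which is the protocol's own baseline and precedes randomisation.
4. Name the sixth questionnaire dimension. This is a minor listing correction.

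The cost is a corrected table, one dimension name and a few sentences of analysis text. No new data are needed, since collected items can be rescored.

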#### Thirty-second sit-to-stand test

Participants will be instructed to cross their arms over their chest and stand in front of a reinforced 44-cm-high chair that is positioned against a wall. They will then sit and stand as many times as possible in 30 s, and the number of repetitions will be recorded.

### Participant timeline {13}

Figure 1 show the recommended SPIRIT figure with the participant timeline.

**Fig. 1 Fig1:**
[figure not shown]
Recommended SPIRIT figure with the participant timeline

### Sample size {14}

GPower 3.1 was used to determine the sample size, assuming a power of 80% and a significance level of 5%. Calculations were based on Herring et al. [37], considering BMI and heart rate as primaries outcomes. This study compared the effects of MICT versus a control group in patients post bariatric surgery. The higher sample size was obtained for the outcome “heart rate.” A total of 17 participants per group were required to detect a significant decrease in the heart rate (effect size = 1.01). However, due to possible dropouts, 25 participants will be included in each group, totaling 75 volunteers.

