### Objectives {7}

This study will aim to determine the effect of MICT and HIIT programs on body composition, cardiopulmonary function, and perceived quality of life in bariatric surgery patients. We will also compare the effects of supervised exercise programs with those of standard follow-up. We hypothesized that both exercise programs would lead to greater improvement in the assessed outcomes than standard recommendations. Moreover, we expect the HIIT protocol to result in greater gains than MICT.

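### The 80% power claim rests on heart rate, which is not a listed outcome, and on one unadjusted MICT-versus-control test, which is not the planned analysis

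*Protocol article*

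**What the plan says.** All references are to the protocol article.

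- **Sample size {14}.** The calculation was run "assuming a power of 80% and a significance level of 5" per cent, "considering BMI and heart rate as primaries outcomes". Its source is one earlier study, described thus: "This study compared the effects of MICT versus a control group in patients post bariatric surgery". Heart rate needed the larger number: 17 per group at an effect size of 1.01. Enrolment is set at 25 per group (75 in total) to cover dropouts. Sidedness, the type of test, any adjustment of alpha and the expected dropout rate are not given.
- **Outcomes {12}.** "Primary outcomes will be (1) body composition, (2) heart rate variability, (3) 6-min walk test results, and (4) perceived quality of life". The secondary outcomes are maximal respiratory pressure, flowmeter, hand dynamometry, the sit-to-stand test and basal metabolic rate.
- **Statistical methods {20a}.** For outcomes that meet the ANOVA assumptions, "a mixed model ANOVA with Bonferroni correction will be used to assess the interaction between group (control group vs MICT vs HIIT) and time". The non-parametric alternative is also Bonferroni-corrected. The number of comparisons is not stated.
- **Objectives {7}.** Both exercise programmes are expected to beat standard recommendations, and in addition "we expect the HIIT protocol to result in greater gains than MICT".

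**The concern.** Two sections name different primary outcomes. Heart rate, which determines the sample size, appears elsewhere only as something monitored during training and recorded before and after the walk test. Heart rate variability is a primary outcome, but it is a different quantity (spectral power of R-R intervals). BMI is not among the variables itemised under body composition.

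The calculation also concerns two groups and one test, while the analysis concerns three groups, three time points and corrected comparisons. The only planning effect is exercise against control, yet a stated hypothesis concerns one exercise programme against the other.

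A reader who takes the 80% at face value would credit the trial with that power for body composition, heart rate variability, walk distance and quality of life, and for each pairwise comparison. The document supports none of these.

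**Working it through.** **Inputs.** From Sample size {14}: d = 1.01, power 80%, alpha 0.05, 17 per group required, 25 per group enrolled. From Statistical methods {20a}: Bonferroni correction, number of comparisons k not stated. Assumptions made here: two-sided testing; k = 3 (all pairwise group contrasts) as the central case, with k = 2 and k = 12 (three contrasts times four primary domains) as the range.

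**Formula.** Two-sample t-test with n per group: df = 2n − 2, noncentrality = d × √(n/2). Power is the probability that a noncentral t exceeds the critical value t(1 − alpha/(2k), df).

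**Step 1: reproduce the stated figure (k = 1).**
- n = 16: noncentrality 1.01 × √8 = 2.857, critical value 2.042, power 78.9%.
- n = 17: noncentrality 1.01 × √8.5 = 2.945, critical value 2.037, power 81.5%.

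So 17 is the first n to reach 80%. Of the other variants tried, a one-sided test gives 13, a Mann-Whitney test by asymptotic relative efficiency gives 18 to 19, and a one-sample or paired formula gives about 8. Only the unadjusted two-sided two-group test gives exactly 17. The arithmetic is correct for that test.

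**Step 2: set the sized outcome beside the listed outcomes.**

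| Used for sizing | Primary outcome? | Secondary outcome? |
|---|---|---|
| Heart rate (drives n) | No | No |
| BMI | No | No |

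None of the four primary outcomes has an effect size or standard deviation in the document.

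**Step 3: keep d = 1.01 and apply the correction.** At n = 17 and k = 3 the noncentrality is still 2.945, but the critical value rises from 2.037 to 2.526.

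| Comparisons corrected | Power, 17 per group | Power, 25 per group | First n reaching 80% |
|---|---|---|---|
| 1 (as calculated) | 81.5% | 94% | 17 |
| 2 | 72% | 89% | 20 |
| 3 | 66% | 86% | 23 |
| 12 | 46% | 71% | 30 |

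For k = 3, n = 22 falls fractionally short (79.97%) and n = 23 gives 82%. Using the error degrees of freedom from all three groups changes little: 68% at 17, and 22 per group needed.

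**Step 4: what this means for dropout.** Going from 25 to 17 allows a loss of up to 1 − 17/25 = 32%. Under three corrected contrasts, 80% at d = 1.01 survives a loss of only 1 − 23/25 = 8% (12% if 22 is enough).

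**Step 5: detectable differences.** Solving for d at 80% power and alpha 0.05/3 gives 1.16 at 17 and 0.94 at 25 per group. Unadjusted, the figures are 0.99 and 0.81.

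**The case against.** The strongest reply has four parts.

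1. *The planned test is an interaction in a mixed ANOVA, not a pairwise t-test.* This stands as a limit on the claim. An omnibus three-group F-test at 0.05 on a single change score, with assumed means of 0, 1.01 and 1.01 standard deviations, has 85% power at 17 per group. With means of 0, 0.505 and 1.01 it has 73%. The correlation between repeated measures is not given, so power for the actual mixed model cannot be computed. A reader might infer that the planned three-arm test lacks 80% power; the document does not show that. It shows only that the 80% was not derived for that test. The directional hypotheses still need pairwise contrasts, which is why Step 3 is relevant.

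2. *Enrolment is 25 per group, not 17.* This also stands. With all 25 evaluable and d = 1.01, the three-contrast figure is 86%. Seventeen is the lowest number that the dropout margin covers, not a forecast, since no dropout rate is stated. The intention-to-treat analysis with imputation is not confined to completers either, although imputation does not restore lost information.

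3. *Nothing shows that HIIT versus MICT has low power.* Correct. One might infer that 1.01 is implausible between two active arms, or that power there is very small. At an assumed d of 0.5 and alpha 0.05/3 it would be 16% at 17 and 25% at 25 per group. But the document gives no effect for this contrast, so both inferences rest on the reader's assumption. Nor does it plan any equivalence claim.

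4. *This is an exploratory pilot.* That removes any demand that every contrast be powered. It does not excuse a formal 80% claim attached to outcomes that the trial does not list.

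**Conclusion.** The point holds, with limits. Without any assumption: the sample size section and the outcomes section name different primary outcomes, and the 80% applies to no listed outcome. The 17 per group matches one unadjusted two-sided MICT-versus-control t-test, not the Bonferroni-corrected three-group analysis.

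The size of the power loss is conditional on d = 1.01 and on the number of corrected comparisons: with three, from about 66% at 17 evaluable per group to 86% at 25; with two, from 72% to 89%. For the four primary outcomes and for HIIT versus MICT, power is unknown, not shown to be low. The error lies in what the calculation is attached to, not in its arithmetic.

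**What to change.** Keep 75 participants and rewrite Sample size {14}:

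- Reconcile it with Outcomes {12}: either drop the description of BMI and heart rate as primary outcomes, or list them as outcomes.
- State the test, its sidedness, the alpha and the number of comparisons that Bonferroni covers, in agreement with Statistical methods {20a}.
- Replace the 80% claim with the standardised difference detectable for the listed primary outcomes. With three corrected contrasts this is 1.16 at 17 and 0.94 at 25 evaluable per group.
- State that HIIT versus MICT will be estimated with a confidence interval and was not used to size the trial.

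The cost is wording only, with no extra participants. The downside is that the stated power becomes less favourable.
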